### 3. Study design

The study is randomized control trials that will be used to determine the efficacy of having patients utilize the asthma module of the interactive website to improve asthma control. Subjects will be randomized to either the intervention (asthma module) or control (preventive module) at the baseline visit.

Overall, the intervention is an interactive website. The website is designed to encourage patients to ask specific questions during visits with their asthma care provider that will help to improve the quality of their care and asthma control. IC subjects will use the asthma module of the interactive website for 12 months, which includes web-based asthma feedback, based on patient self-report. The feedback suggests questions to ask during visits with asthma care providers, reasons for asking the questions and links to other trustworthy websites that support the message. The website will be used a) each month and b) before visits with asthma care providers. When using the website routinely each month, the subject will report on their asthma control as well as clarify the date of their next asthma care provider visit. This allows the website to remind patients to use the website before doctor visits as well as to suggest that patients make a sooner visit, in keeping with the 2007 NAEPP Guidelines (page 345), if their asthma is not controlled and their next scheduled visit is far in the future.

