### 5. Procedures to be followed

Potentially interested participants will call a toll-free number and speak to a study coordinator, who will complete a phone screener. The phone screener includes questions in the following categories: basic demographic information, race and ethnicity, exclusion criteria questions, contact information (e.g., phone number) and social security information, so that we are able to mail compensation for participation in the study. Data from this phone screening process will be collected on paper and parts of this form will be later entered into the management module. During this phone screener, the study coordinator will explain the study, ask questions to determine eligibility and then ask once again if the patient may be interested in participating. If the participant is eligible and interested, the study coordinator will read the verbal consent document over the phone. If the participant is interested, eligible and consents to participate in the study over the phone, the study coordinator will inform the participant that he/she is included in the study and will receive an email within the next day from the study, explaining what will happen next. The coordinator will also inform the participant that upon logging into the application for the first time, they will have to read, review, and electronically agree to a Member Authorization Form by Highmark. They will be able to print out this form for their own records. Those that do not agree will not be allowed to participate. Those that do agree will then be randomized automatically, according to an algorithm written in the management module, to either the asthma or preventive care modules. The study coordinator will enter the specific screening information into the application (all screening fields except for mailing address and SSN) after their phone call with the participant and then check a box representing that the participant has completed the phone consent procedure. The participant will then be asked to use the website once every 30 day cycle and within 14 days of their next scheduled visit with their asthma care provider. At baseline, 6 months, and 12 months, they will be asked to complete specific measures online, as outlined below. During other monthly logins, they will be asked to complete short surveys that will then generate feedback based on their group they were randomized to. Women of child bearing potential will be asked monthly if they are currently pregnant and if they state that they are, they will be withdrawn from the study. At the close of the study, Penn State researchers will be authorized to provide Highmark with the names, DOB’s, gender and dates participants electronically agreed to the Member Authorization Form. Highmark will then provide Penn State researchers with access to claims data for all enrolled participants, for the 2 years prior to study participation and up to 2 years post enrollment. Asthma-related claims of hospitalization, outpatient visits, emergency department visits and medications will be examined.

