Controller to reliever ratio: There are generally two types of medicines for asthma; those used for quick relief of asthma symptoms (“relievers”), and those that are used daily to prevent asthma symptoms (“controllers”). Using a controller medication is the first step in managing persistent asthma, according to the treatment algorithm (page 343) on the 2007 NAEPP Guidelines 26, and has served as a main outcome measure in many quality improvement studies 66-68,104. By using more controller medicines, therefore, the number of reliever medicines tends to go down 105. The ratio of controller/reliever canisters is strongly predictive of future emergency department visits and, as such, has been used as a measure of asthma control and quality of care 105-107. As the intervention is designed to help individuals receive a controller medicine and, for those whose asthma is not controlled, often a second controller medicine, the controller to reliever ratio should be sensitive measure of the effects of the intervention. We will use standard ways to express this variable, which will be calculated as the ratio of the number of controller medications (i.e., inhaled corticosteroid) dispensed during the study year divided by the sum of the number of controller medications dispensed plus the number of canisters of inhaled relievers (e.g., short-acting beta-2-agonists) dispensed during the study year. This ratio ranges from 0 (no controller medications) to 1.0 (no reliever medications) 105-108. Grymonpre and colleagues observed that the concordance between claims data on medication acquisition and pill counts was between 79% and 88%, which were both highly significant 109. This data will be captured in the electronic claims data from Highmark, as none of the medicines are inexpensive, so patients should find it less expensive to use their prescription drug coverage through Highmark than to pay out of pocket. Similar methods are used by the National Committee for Quality Assurance to estimate the quality of asthma care in over 500 health plans nationally 7.

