### 7. Statistics and sample size justification

Sample size considerations focus on the primary hypothesis posited in the Specific Aims section. The major research goal is to determine the efficacy of having patients use the asthma module of the interactive website, for a period of 12 months, for improving asthma control. The primary outcome will be asthma control, based on the Asthma Control Test (ACT), a valid and reliable 5-question self-report measure of asthma control. 98-100. We chose to power the study based on asthma control, as it is a powerful predictor of emergency department visits, activity limitations and missing days of work due to asthma 6,100,130, and it is a central goal in both Healthy People 2010 as well as in the 2007 NAEPP Guidelines 26,131. We chose not to power the study on improving the use of controller medications, such as inhaled corticosteroid use, as the rates of use of these medications has increased greatly over the past decade, which would lead to a ceiling effect 7. Despite the broad use of these controller medications, however, asthma control rates are still in the 50% range, so we will not suffer from such a ceiling effect 5. Our estimated baseline rate of 55% is based on two studies of asthma control in similar groups of insured patients that both showed asthma control rates in the 50% range 5,6. For example, Schatz and colleagues observed that 48.4% of 570 insured adults with asthma had an Asthma Control Test (ACT) score of less than 20, the same measure of asthma control that we are using in the current study 5. Vollmer and colleagues reported that 48% of 5,181 insured adults with asthma reported good asthma control, using a slightly different measure of asthma control, the Asthma Quality of Life Questionnaire 6. We expect a slightly higher baseline control rate, as patients who volunteer for clinical trials tend to be healthier than those who do not 132. This expected effect size is based on a meta-analysis by Stone and colleagues that examined the efficacy of reminders, given to patients, on rates of adult immunization and cancer screening services 16. Patient reminders, similar to what we plan to use in the current study, significantly increased immunizations (odds ratio, OR=2.5), mammography utilization (OR=2.3), cervical cytology screening (OR=1.7) and colon cancer screening (OR=2.8). These effect sizes are consistent with reviews by other investigators 23,50,133. In the current study, we will be powered to detect an effect size that translates to a relative risk of 1.3 (0.70 /0.55) and odds ratio of 1.9. We chose this conservative effect size to address the fact that we are not examining a process of care but an outcome of care. While we expect the intervention to lead to increases in the number of controller medications used, additional medications do not always help patients. Also, we need to be sensitive to the possible differences in efficacy between interventions to increase adult preventive services (e.g., pap testing) and studies such as ours that seek to change chronic disease management practices. We considered powering on a numerical change in the Asthma Control Test (ACT), our main outcome measure, but chose not to do this as there is less consensus about what represents a meaningful change in the ACT than there is about what represents appropriate asthma control 5,98. We will, however, analyze changes in the ACT as a continuous variable, in our secondary analyses. Formulas based on the chi-square test were used to derive sample size calculations from the following assumptions. We assume a type I error rate (alpha) of 5% (0.05), 80% (0.80) power, and a two-tailed test, which allows us to detect significant differences in either direction. We expect a 12-month retention rate of 80%, although we believe that our procedures will substantially minimize the likelihood of attrition. We considered randomizing providers but felt that, given the number of providers in the two geographical areas, it was very unlikely that a physician would have more than one subject enrolled in the study. We will, however, track the name of the asthma care provider, so that we can include this variable in a sensitivity analysis, to be certain that adding this variable does not change the conclusions of the data analyses. In order to achieve 80% power to detect a difference of 70% vs. 55% between intervention and control group, we will need to randomize 408 patients into the two conditions at baseline. This assumes that no more than 20% are lost to follow-up at 12 months, leaving no fewer than 326 subjects available for analysis at the end of the study. We do concede, however, that smaller differences in asthma control may be clinically important, particularly on a population level. To power the study on a 10% difference in asthma control, however, we would have needed to recruit 940 subjects, which we felt would unnecessarily increase the cost and complexity of the study.

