
Preliminary data analysis plan: All analyses will be conducted using SAS Version 9. Initially, descriptive statistics such as the minimum, maximum, range, median, quartiles, mean, and standard deviation for each continuous variable and frequencies and percentages for each categorical variable will be used to summarize all variables as well as detect outliers, data entry mistakes, and missing values. These descriptives will be used to “clean” the data prior to analysis. Exploratory graphical techniques will be used to further examine these data. The normality of the distribution of mediators of interest, both in their original and transformed state (if necessary), will be examined with a normal probability plot when applicable. Longitudinal plots will be used to identify trends over time that are both population- and individually-based.

Differential dropout and attrition: Initially, the two randomized groups will be compared on important demographic and other baseline variables to ensure successful randomization. If it is determined that the groups, by chance, are significantly different on some measures, we will include those theoretically meaningful confounders as covariates in subsequent analyses. T-tests, ANOVA, and/or chi-square tests of independence comparing those who complete the study with those lost to follow-up will be performed on baseline demographic variables, asthma control, asthma-related quality of life, and baseline use of controller medications to identify potential differential dropout. These comparisons ensure equality of intervention and comparison groups after accounting for study attrition. For the primary outcome, we will apply intention to treat (ITT) principles with all available data included in the first set of analyses 134. Second, subjects lost to follow-up will be conservatively assumed to have not changed their level of asthma control between baseline and 12 months. Similar findings between both approaches would increase confidence in the results overall.

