Analyses of mediating and moderating processes: The analytic procedures outlined provide a convenient way of identifying effect modifiers and confounders, while modeling the underlying relationship of interest. As noted in the analytic plan for the primary outcome, the analysis of moderators will be undertaken by creating interaction terms between treatment and covariates of interest, such as asthma-related quality of life 139, health literacy and socio-demographic characteristics. We will also examine the effects of treatment fidelity and intervention dosage (e.g. number of visits to web site, total time spent on web site) as potential moderators of intervention efficacy. Mediational analyses will be conducted in the form proposed by Baron and Kenny 140. Briefly, this entails four steps in which it is demonstrated that there is: a) a significant association between the independent variable and the dependent variable; b) a significant association between the independent variable and the mediators; c) a significant association between the mediator and outcome; and d) a meditational effect is argued to occur when a significant decrease in the relation between the independent (e.g. treatment) and dependent (e.g. asthma control) variables upon the forced entry of the proposed mediators into the model at the final step. We will examine each mediator separately, as joint estimation makes estimation and interpretation of the effect of each potentially mediating variable problematic. Data for these analyses will be obtained from online surveys, date stamps from the interactive website and from the timing of physician visits from chart reviews. For example, we can test whether use of the interactive website influences use of other asthma controller medications (e.g., salmeterol). However, we will also explore various temporal combinations between the exogenous (treatment), endogenous mediators (asthma specialist visits) and outcomes and we will pay particular attention to the temporal ordering of key events and measurement periods.

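### The mediation steps name no adjustment for prior asthma control, which triggers the website's prompts and predicts the outcome, so the mediator–outcome link is open to confounding whose direction differs by mediator

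*Protocol*

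**What the plan says.** Protocol Section III.6 (Mediating Variables) hypothesises that every listed mediator carries the effect of the intervention. The list includes outpatient asthma visits, the controller-to-reliever ratio and medication adherence.

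Section III.7 (Analyses of mediating and moderating processes) fixes the test as the four Baron–Kenny steps. Step (c) is "c) a significant association between the mediator and outcome". Step (d) looks for a drop in the treatment effect once the mediator is entered. No covariate is named for either step.

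Two passages say who is steered towards the mediators. Under Section III.3 the website will "suggest that patients make a sooner visit, in keeping with the 2007 NAEPP Guidelines (page 345), if their asthma is not controlled" and the next visit is distant. Section III.6 says the intervention is meant to secure a controller and, "for those whose asthma is not controlled, often a second controller medicine".

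The covariate criterion is in Section III.7 (Differential dropout and attrition): "If it is determined that the groups, by chance, are significantly different on some measures, we will include those theoretically meaningful confounders as covariates". The paragraph on the main outcome also speaks of baseline differences between the groups.

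The data for a better adjustment are already planned. ACT is taken at baseline, and claims will be supplied "for the 2 years prior to study participation and up to 2 years post enrollment".

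**The concern.** Randomisation protects the arm-to-mediator and arm-to-outcome comparisons. It does not protect the mediator-to-outcome comparison, because patients are not randomised to visits or to drug use. Here the intervention's own rules link poor control to more visits and more controllers, and poor control also plausibly lowers the chance of ACT ≥ 20 at 12 months. This is confounding by indication.

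The between-arm criterion does not address it. Baseline control is expected to be balanced between arms, so the criterion would normally leave it out, yet within each arm it can still confound mediator and outcome.

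At stake is the explanation of how the website works. Real mediation through visits could be missed, and mediation through the controller-to-reliever ratio could be claimed where there is none.

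**Working it through.** **1. The plan's own figure.** The protocol gives no calculation for mediation, so the check takes its analysable sample size. Inputs from Section III.7: "We assume a type I error rate (alpha) of 5% (0.05), 80% (0.80) power, and a two-tailed test"; "In order to achieve 80% power to detect a difference of 70% vs. 55% between intervention and control group"; "Formulas based on the chi-square test were used to derive sample size calculations". Equal allocation is assumed.

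n per arm = [1.96·√(2·0.625·0.375) + 0.8416·√(0.70·0.30 + 0.55·0.45)]² / 0.15² = (1.342 + 0.569)² / 0.0225 ≈ 162.3, so 163. The total is 326, and 326/0.80 = 407.5, so 408. The protocol's 326 and 408 reproduce.

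**2. Binary mediator such as a prompted visit.** All parameters are assumed.
- Severity U is standard normal, and about 45% of patients are uncontrolled.
- Log-odds of the mediator = −1.2 + 0.8·uncontrolled + 1.5·(asthma module × uncontrolled). This gives about 23% if controlled, 40% if uncontrolled in the control arm, and 75% if uncontrolled in the asthma arm.
- Log-odds of 12-month control = 0.25 + b·M − s·U, with no direct treatment effect.
- Odds ratios come from 400,000 subjects; detection comes from 500 trials of 326.

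True mediator odds ratio 2.0:

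| s | OR, no adjustment | OR, arm only | OR, arm + severity | OR, arm + baseline measure correlated 0.6 with severity |
|---|---|---|---|---|
| 0.5 | 1.47 | 1.45 | 2.01 | 1.62 |
| 1.0 | 1.09 | 1.07 | 2.02 | 1.28 |
| 1.5 | 0.83 | 0.82 | 2.00 | 1.03 |

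Detection below is for s = 0.5 / 1.0 / 1.5.
- True OR 2.0: step (c) is positive and significant in 38% / 7% / 0.4% of trials unadjusted, against 78% / 72% / 62% adjusted for arm and severity. It is significantly reversed in 0% / 2% / 11% unadjusted.
- True OR 2.7: 80% / 30% / 4% unadjusted, against 97% / 95% / 91% adjusted.
- True OR 1: a false harmful association appears in 21% / 59% / 83% unadjusted, against 3% to 4% adjusted.

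Step (d) is distorted too. With s = 1.0, true OR 2.0 and full mediation, the treatment coefficient falls only from 0.108 to 0.097 without severity. With severity it falls from 0.124 to 0.001.

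**3. Visit counts, N = 326 (assumed inputs).** Baseline control is 55%. Control at 12 months is 75% if controlled at baseline and 31% if not. Mean visits are 2 and 3, with 1.5 added in uncontrolled asthma-module patients.
- No visit effect: step (c) rejects in 90% to 95% of trials across repeated runs, in the direction of more visits and worse control. With baseline control included, a run gave 2%.
- Visit effect +0.3 log-odds per visit: the arm-to-visits and visits-to-control links are jointly detected in 3% to 8% of trials without baseline control and 90% to 95% with it.
- No excess visits among uncontrolled usual-care patients (control 70%/37%, mean visits 2/2): 79% to 82% without, 92% to 94% with. The loss is only about 12 to 13 points.
- Control status redrawn after baseline for 30% of patients: even with baseline control in the model, false rejection is 52% to 58% and detection 43% to 48%.

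**4. Controller-to-reliever ratio.** Section III.6 defines it as controllers / (controllers + relievers). Rescue-inhaler use is an ACT item, so uncontrolled patients tend to have a lower ratio and a worse outcome. Assumed: mean relievers 2 if controlled and 5 if not, mean controllers 6, plus 1.5 prompted in uncontrolled asthma-module patients, and no true effect. Step (c) was positive and significant in 96% of trials and never negative; a separate run gave 99%. The figure falls when baseline control predicts the outcome less strongly.

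**The case against.** The protocol nowhere says the association will be unadjusted. Its account of the four steps is a summary. The same paragraph says the procedures help identify confounders and that the time order of events will be examined, and the main-outcome paragraph names asthma symptoms as a possible covariate. A covariate list may sit in a statistical analysis plan that is not shown. This stands as far as it goes: the absence of adjustment is read from what the text specifies. It does not remove the point, because the protocol does state a criterion for choosing covariates, and that criterion looks at the wrong imbalance.

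A reader might infer that the test hides or reverses mediation in general, or merely measures who was ill enough to be prompted. The documents do not support that, for these reasons:
- With weak confounding and a strong mediator, step (c) still succeeds in about 80% of trials. Clear reversal needs strong confounding. The test mixes need with any real effect.
- For the ratio, which is how the protocol expresses controller use, the bias plausibly runs the other way.
- Section III.6 ties the specialist-visit suggestion to patients who have not yet seen one, not explicitly to uncontrolled asthma.
- The size depends on how much more often uncontrolled patients attend in usual care. No figure is given, and the protocol itself describes clinical inertia there.
- The joint-detection figures leave out step (a), a significant total effect. In the visit example, requiring it changes 8% against 93% to 6% against 43%.
- With no true visit effect, the false associations are negative, so they are not false findings of mediation through visits.

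Mediation is hypothesised in Section III.6 but is not among the Specific Aims.

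**Conclusion.** The point holds as a limited one. As specified, steps (c) and (d) are open to confounding by asthma control, and the between-arm criterion does not deal with it.

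For provider visits the bias is against mediation. Under the assumptions used, it runs from mild attenuation (2.0 to 1.47) through near-null (1.09) to reversal when confounding is strong (0.83). For the controller-to-reliever ratio the plausible result is spurious mediation. These sizes illustrate the range and do not predict this trial, since the protocol gives no figure for visit rates by control status, reliever use, or how strongly baseline control predicts 12-month control.

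Baseline ACT is a real improvement but only a partial cure, because control reported after baseline also drives the prompts. The primary comparison of randomised arms is untouched.

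**What to change.** In Section III.7 (Analyses of mediating and moderating processes), state that:
- the mediator models include treatment arm, baseline ACT and, for claims-based mediators, the pre-enrolment value of the same mediator, whether or not the arms differ on them;
- the between-arm imbalance criterion does not select covariates for these models;
- mediator–outcome results are reported as associations, with a sensitivity analysis for residual confounding.

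Control measured after baseline is itself affected by treatment. If it is used, it needs a method for time-varying confounding and cannot simply be entered as a covariate. The ACT schedule should also be reconciled: Section III.6 and the schedule table give baseline, 6 and 12 months, while the main-outcome paragraph of Section III.7 says every three months. This decides which pre-mediator control data exist in both arms.

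The cost is a few sentences, a few extra covariates and some added analysis. Baseline ACT and pre-enrolment claims are already to be collected.
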